# Telephone-based goal management training for adults with mild traumatic brain injury: study protocol for a randomized controlled trial

**DOI:** 10.1186/s13063-015-0775-1

**Published:** 2015-06-02

**Keywords:** Randomized trial, Traumatic brain injury, Cognitive rehabilitation, Goal management training, Mindfulness

## Abstract

**Background:**

Approximately 1 million individuals experience a mild traumatic brain injury (TBI) and cost the United States nearly $17 billion each year. Many trauma survivors with mild TBI have debilitating and long-term physical, emotional, and cognitive impairments that are unrecognized at trauma centers. Early intervention studies are needed to address these impairments, especially cognitive deficits in executive functioning. Goal management training (GMT) is a structured cognitive rehabilitation program that has been found to improve executive functioning in patients with moderate to severe TBI. The current study adapted the GMT program for telephone delivery in order to improve the accessibility of rehabilitation services in a patient population with multiple barriers to care and significant yet unrecognized cognitive impairment. The primary objective of this study is to examine the efficacy of telephone-based GMT for improving executive functioning, functional status, and psychological health in trauma survivors with mild TBI.

**Methods/design:**

This study is a three-group randomized controlled trial being conducted at a Level I trauma center. Ninety trauma survivors with mild TBI and cognitive deficits in executive functioning will be randomized to receive telephone-based GMT, telephone-based education, or usual care. GMT and education programs will be delivered by a physical therapist. The first in-person session is 1 h and the remaining six telephone sessions are 30 min. A battery of well-established cognitive tests will be conducted and validated questionnaires will be collected that measure executive functioning, functional status, and depressive and posttraumatic stress disorder symptoms at 6 weeks, 4 months, and 7 months following hospital discharge.

**Discussion:**

This study supports a telephone-delivery approach to rehabilitation services in order to broaden the availability of evidence-based cognitive strategies.

**Trial registration:**

This trial was registered with Clinicaltrials.gov on 10 October 2012, registration number: NCT01714531.

## Background

Approximately 2.5 million individuals are hospitalized each year due to traumatic injuries [1, 2], with over half experiencing a brain injury. Patients with moderate to severe traumatic brain injury (TBI) have evident debilitating cognitive and functional impairments. However, mild TBI is a silent epidemic that can result in long-term or permanent impairment and disability that is under-managed at trauma centers [3, 4]. The Centers for Disease Control (CDC) estimates that more than 1 million individuals experience a mild TBI and cost the United States (U.S.) nearly $17 billion each year [4].

There are considerable symptoms as a consequence of mild TBI including poor concentration, lethargy, confusion, disorientation, and irritability [5]. Physical, emotional, and cognitive deficits as a result of these symptoms can become chronic and disabling leading to vocational and social disabilities [5]. Physical symptoms such as impaired gait, persistent headaches, fatigue, and dizziness may continue for several months up to many years, delaying one’s ability to return to work [6, 7]. Depressive and posttraumatic stress disorder (PTSD) symptoms are extremely common in individuals with cognitive impairment [8, 9], with mild TBI being the triggering event for an episode of depression in some individuals [10]. Thirty to forty percent of trauma survivors with mild TBI have depressive symptoms and 20 % to 30 % have PTSD within the first year of recovery. Long-term cognitive consequences of mild TBI include deficits in attention, memory, and most importantly, executive functioning [11, 12, 7].

Executive functions are those involved in complex cognitions such as planning, initiating activities, and monitoring and inhibiting, which enable individuals to engage in purposeful, goal-directed behaviors (for example, balancing a checkbook and understanding social cues) [13, 14]. Deficits in executive functioning are the most disabling of all cognitive impairments and affect a person’s ability to manage effectively in one’s personal and professional life. Current literature demonstrates that deficits in executive functioning contribute to reduced quality of life, difficulty in returning to work, and persistent psychological distress in patients following head injury [15, 16]. Deficits in executive functioning may also contribute to the development and maintenance of depression and PTSD [17], with studies suggesting that cognitive impairment and psychological distress share neuroanatomic and pathophysiologic correlates [17, 18].

Current literature supports the effectiveness of cognitive rehabilitation for improving cognitive, functional, and psychological health in patients with identified brain injury [19, 20]. Cognitive rehabilitation retrains previously learned skills, increases awareness and acceptance of cognitive impairments, and teaches self-confidence and self-efficacy for coping with emotional distress. Data show that cognitive interventions are effective in a variety of settings (for example, inpatient, outpatient, and home) and when delivered by various professionals in different disciplines [21, 20]. Cognitive rehabilitation has not been traditionally offered or studied in patients with mild TBI. This population of trauma survivors has limited access to care due to underdiagnosis, as well as financial constraints and mobility issues that typically render clinic-based rehabilitation impractical.

Goal management training (GMT) is a structured form of cognitive rehabilitation that has been found to improve executive functioning in patients with moderate to severe brain injury and older adults with cognitive impairment [22, 23]. GMT uses metacognitive strategies to improve patients’ ability to organize and achieve goals in ‘real-life’ situations. GMT participants are taught to be reflective (that is, to ‘stop and think’) prior to making decisions and executing specific tasks, and to achieve success by dividing tasks into manageable units, so as to increase the likelihood that these tasks are completed.

The purpose of this study is to examine the efficacy of a telephone-based GMT program for improving executive functioning, functional status, and depressive and PTSD symptoms in trauma survivors with mild TBI. The GMT program will be compared to a telephone-based education program and usual care at 4 months (treatment completion) and 7 months following hospital discharge. Emerging research suggests that telephone rehabilitation may be a feasible and effective alternative (with much broader applicability) to clinic-based interventions [24–27]. Researchers have also suggested that rehabilitation conducted in a patient’s well-known and natural environment may facilitate and enhance the transfer of skills to the everyday living setting [28].

## Methods/design

### Study design

This study is a three-group randomized controlled trial conducted at a Level I trauma center. Figure 1 depicts the overall study design with assessments at 6 weeks (baseline) and 4 and 7 months after hospital discharge (see ClinicalTrials.gov and NCT01714531 for more information). The investigators, participating surgeons, research personnel conducting the assessments, and patients will be blinded to group assignment. Potential subjects will be informed that they will be randomly assigned to one of two different educational treatments or usual care. Participants will be asked not to discuss study procedures with their treating surgeon, medical staff, and research personnel.

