### Randomization

Participants will be randomized to one of the three groups (telephone-based GMT, telephone-based education, usual care) in a 1:1:1 ratio. Block size will be determined randomly with the patient as the unit of randomization. A randomization list will be computer generated and administered thought the REDCap system. Randomization will occur immediately after the baseline assessment at 6 weeks. Surgeons and research personnel conducting the assessments will be unaware of group assignment.

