### Interventions

#### Telephone-based GMT

The telephone-based GMT program will include seven sessions delivered by a physical therapist (Table 2). GMT was originally conceptualized by Robertson [33] and derived from Duncan’s [34] theory of goal neglect. Levine and colleagues expanded on GMT and tested a standardized protocol and treatment manual in patients with moderate to severe brain injury and in older adults with cognitive impairment [23, 35, 36, 21]. The GMT intervention targets cognitive deficits in executive functioning that impact a person’s ability to carry out daily tasks. This current study has adapted the GMT intervention to include mindfulness techniques [37] and to be delivered over the telephone, in collaboration with [name]. The first session is 1 h and conducted in-person to provide participants with a session-by-session treatment manual. The remaining six sessions are 30 min and are conducted once a week over the phone. Sessions focus on increasing awareness of one’s thoughts and experiences and increasing self-efficacy. Participants learn how to use mindful attention and goal setting to recognize and stop ‘absentmindedness’ and ‘automatic pilot’ in order to reduce daily errors and ‘slips’ (Fig. 2). Each session builds upon the content of the previous session. Weekly homework is personally tailored based on patient goals.

**Table 2 Tab2:** Summary of goal management training intervention by session

Session 1: Slip-ups	Overall introduction, define goals and absentminded slips, raise awareness of consequences of slips, introduce present-mindedness and mindful practice in daily life
Session 2: Stop the automatic pilot	Define automatic pilot and how it leads to errors, learn how to ‘STOP’ automatic pilot, practice present-mindedness
Session 3: The mental blackboard	Define the mental blackboard, learn how to ‘STOP’ and check mental blackboard, staying in the present through breathing
Session 4: State your goals	Define goals, learn how to state goals, practice ‘STOP’ and ‘STATE’ and breath focus to become present-minded
Session 5: Making decisions	Define competing goals, learn how to understand emotional reaction to indecision, practice ‘STOP-STATE’ to reduce stress and indecision
Session 6: Splitting tasks into subtasks	Define overwhelming goals, learn how to split goals, practice ‘STOP-STATE-SPLIT’

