#### Telephone-based education

The telephone-based education group will receive an educational program that is matched to the GMT intervention in terms of session length and contact with the study therapist. The education program includes seven sessions delivered by a physical therapist (Table 3). Material was developed by Levine *et al*. [23] based on material commonly employed in rehabilitation centers and has been successfully used in several studies as a comparison to the GMT intervention [35, 38]. Sessions address education on brain function and cognitive principles of memory, attention, language, perception, and motor skills. Education on stress reduction, sleep hygiene, energy management, exercise, communication, and nutrition are also provided. The first session is conducted in-person to provide participants with a session-by-session treatment manual. The remaining six sessions are conducted once a week over the phone.

**Table 3 Tab3:** Summary of education intervention by session

Session 1: Introduction	Overall introduction, explain the goals of the program, define basic brain anatomy and consequences of trauma
Session 2: Brain activity	Explain importance of keeping brain active, define the assessment of brain activity
Session 3: Memory I	Explain the importance of memory, define the types of memory and memory processes
Session 4: Memory II	Review memory and the brain, learn how memory breaks down, define functional implications of memory loss
Session 5: Attention and executive function	Define attention and executive functioning, learn how attention and executive functioning breaks down
Session 6: Lifestyle I	Explain importance of stress, sleep, and exercise on brain function, define the influence of lifestyle on recovery
Session 7: Lifestyle II	Explain importance of nutrition, energy management, and communication on brain function, review healthy lifestyle for recovery, wrap-up

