#### Usual care

Participants in the usual care group will receive usual care as determined by the treating surgeon. Usual care may include referral to a physical therapist, occupational therapist, psychiatrist, and/or psychologist. At the end of the intervention phase, participants will be asked whether they had, on their own initiative, followed a course to improve their cognitive functioning.

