### Quality assurance

One study physical therapist will complete training in both the GMT and education programs. Formal training will occur with the principal investigator (PI) of the study ([name]) and an experienced neuropsychologist ([name]). Written and skills competency tests will be completed at the end of training. After passing both tests (scores >85), the GMT and education treatments will be implemented with study staff and a pretest of both programs will occur with one patient. All sessions during the pretest will be audiotaped and reviewed to evaluate adherence to the treatment protocol and structured manual.

Our treatment integrity protocol includes detailed session-by-session treatment manuals for the telephone-based groups and ongoing supervision to ensure accurate and consistent treatment delivery (provided via weekly clinical team meetings). The study physical therapist’s adherence to procedures will be assessed by audio recording all sessions and randomly selecting sessions for the investigators to review using standardized fidelity checklists. The study physical therapist will also complete a checklist of all the components delivered during each session and make note of any protocol deviations. If the integrity of the treatments is compromised, the study therapist will be retrained and 100 % of audiotapes will be reviewed until problems are addressed.

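### The stated blinding of patients and investigators cannot hold as written: patients can be masked at most between the two telephone programmes, so patient-reported comparisons with usual care are not patient-blinded

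*Protocol article*

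**What the plan says.** All references are to the protocol article.

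- **Study design** makes an unqualified claim covering four groups: "The investigators, participating surgeons, research personnel conducting the assessments, and patients will be blinded to group assignment". The next sentence gives what patients are told: "Potential subjects will be informed that they will be randomly assigned to one of two different educational treatments or usual care". Patients are also asked not to talk about study procedures with their surgeon, medical staff or research personnel.
- **Randomization** gives a shorter list: "Surgeons and research personnel conducting the assessments will be unaware of group assignment". Patients and investigators are not mentioned there.
- **Telephone-based GMT**: "The telephone-based GMT program will include seven sessions delivered by a physical therapist". The first session is in person and comes with a manual; six weekly telephone sessions follow.
- **Telephone-based education** also has seven therapist sessions and is described as "matched to the GMT intervention in terms of session length and contact with the study therapist".
- **Usual care**: "Participants in the usual care group will receive usual care as determined by the treating surgeon", and "Usual care may include referral to a physical therapist, occupational therapist, psychiatrist, and/or psychologist". No study sessions, manual or study-therapist contact are described.
- **Quality assurance** provides for recording all sessions and "randomly selecting sessions for the investigators to review using standardized fidelity checklists".

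**The concern.** Blinding is asserted for two groups whose place in the design does not allow it in full. A patient who knows that usual care is an option, and who either does or does not receive therapist sessions, can work out on which side of that divide he or she falls. An investigator who scores a recording hears which programme is being delivered.

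The patient side matters more. Comparison of GMT with usual care at 4 and 7 months is a stated purpose (end of Background), and DEX and CFQ, both described as patient-reported, are among the primary measures. When the patient supplies the rating, masking the person who collects it does not remove the influence of knowing one's own assignment. Expectation, and the experience of receiving attention, can then enter the difference from usual care. If the Study design sentence is taken at face value, a questionnaire difference from usual care would be read as a patient-blinded result, which this design cannot provide.

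**Working it through.** No figure in the document is at issue, so the check sets the passages side by side, role by role.

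**1. Patients, either programme against usual care.**
- Known before randomization: the options are two educational treatments or usual care (Study design).
- Experienced after randomization: seven therapist sessions and a manual in GMT and in education; nothing of the kind described in usual care.
- Result: a patient with no study sessions can infer usual care, and a patient with sessions can infer that it is not usual care. Blinding is not possible for this contrast.

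**2. Patients, GMT against education.**
- Both are presented to patients as educational treatments, and the two are matched on session length and therapist contact.
- Result: masking as to which programme is under test is feasible, and the document supports it.

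**3. Investigators.**
- Investigators review randomly selected recordings with fidelity checklists (Quality assurance).
- Tables 2 and 3 show plainly different content: stopping automatic behaviour, stating and splitting goals in GMT; brain function, memory and lifestyle teaching in education.
- Result: a reviewing investigator can tell the arm of each sampled telephone session. Usual care generates no recordings. The document does not say whether reviewers can identify the patient.

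**4. Surgeons and assessors.**
- Study design and Randomization agree that they are masked, and the request not to discuss procedures supports this.
- Result: nothing found against it.

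**5. Which outcomes are exposed.**
- Table 4 lists seven primary instruments: five performance tests (D-KEFS Tower, Trails B, FAS, SART, Hotel Task) and two patient-reported questionnaires (DEX, CFQ); 5 + 2 = 7.
- The secondary outcomes are four questionnaires: FAQ, QOLIBRI-OS, PHQ-9 and PCL-C. The article says that patients rate the PCL-C; PHQ-9 and QOLIBRI-OS read naturally as the patient's own ratings. It does not say who completes the FAQ.
- Result: at least DEX, CFQ and PCL-C, and most likely PHQ-9 and QOLIBRI-OS, are rated by someone who knows whether he or she is in usual care.

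**6. Size.** The article gives no standard deviations for the questionnaires and no information on expectation effects. No magnitude of bias can be derived from it, and none is claimed here.

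**The case against.** The strongest reply is that this is one loosely worded sentence in an otherwise sound three-arm design. An unmasked usual-care arm beside an attention-matched control is a normal arrangement, and the education arm exists to deal with attention and expectation. That is right, and it is why the point concerns the blinding claim and the reading of certain contrasts, not the choice of arms. It does not rescue the sentence, because usual care remains a named comparator.

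A second reply is that the ordering of contrasts commonly belongs in the analysis plan, which is not shown. That also stands: its absence from the article is not a fault. The blinding statement, however, is in the article and is wrong there.

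Several stronger readings are tempting, but the documents do not support them:

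- *That usual care has no contact.* These patients attend the same assessments and may be referred to several kinds of clinician. What they lack is contact with the study therapist.
- *That all investigators know all assignments.* Training one therapist in both programmes reveals nobody's arm, and the article does not say who attends the weekly team meetings or whether individual patients are discussed there. Only the recording review carries weight, and only for those who review and the sessions sampled.
- *That the Randomization section contradicts Study design.* It names fewer roles and says nothing about the others. It is narrower, not opposed.
- *That the trial as a whole is open-label.* Surgeon and assessor masking is unaffected, and patients may still be masked between GMT and education.
- *That the bias can be quantified.* Any figure would rest on assumptions from outside the document.

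**Conclusion.** The blinding statement in Study design is wrong as written. Patients can be masked at most between GMT and education; against usual care they cannot be. Investigators who review recordings are not masked to the arm of the sampled telephone sessions. Consequently, patient-reported outcomes, including the primary DEX and CFQ, are not patient-blinded in the comparison with usual care. The five primary performance tests keep their assessor masking as far as the document shows.

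This rests on two readings of the text: that usual-care patients receive no study-therapist sessions, since none are described, and that a recording's content identifies the programme, which Tables 2 and 3 make hard to doubt. The size of any bias is unknown. The consequence is for what may be concluded from the usual-care contrast on self-report, not for the validity of the trial as a whole.

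**What to change.** 1. In Study design, replace the single sentence with blinding by role: surgeons and outcome assessors masked; patients masked only between GMT and education; the study therapist and the investigators who review recordings not masked.
2. Align the Randomization section with that list.
3. Before the analysis plan is approved, state that patient-reported contrasts against usual care are unblinded to the patient and will be interpreted as such, and that the attention-matched GMT versus education contrast is the better protected one for those outcomes.

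By the article's own account this is still feasible: recruitment is complete, follow-up is continuing, and the analysis plan is to be finalised before data collection ends. The cost is a change of text. Treatment, visits and sample size are untouched. The small downside is that the usual-care contrast carries less weight for self-report outcomes.

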**Figure 1 Fig1:**
[figure not shown]
Study flow diagram

### Study population

Ninety English-speaking adults with mild TBI and cognitive deficits in executive functioning who are admitted to a Level I trauma center will be recruited for this study. Mild TBI will be determined through a medical chart review and patient interview questions using American Congress of Rehabilitation Medicine guidelines [29]. The guidelines include at least one of the following: (1) any period of loss of consciousness; (2) any loss of memory for events immediately before or after the accident; (3) any alteration in mental state at the time of the accident; and (4) focal neurological deficit(s) that may or may not be transient; but where the severity of the injury does not exceed the following: (1) posttraumatic amnesia not greater than 24 h; (2) after 30 min, an initial Glasgow Coma Scale of 13 to 15; and (3) loss of consciousness of approximately 30 min or less. Eligible participants with mild TBI will also be screened for presence of cognitive deficits in executive functioning. Deficits are defined for this study as one standard deviation (SD) below the norm referenced mean on any one of the following neuropsychological tests: Delis-Kaplan Executive Function System (D-KEFS) Tower Test, Trail Making Test B (Trails B), and FAS test [13, 30].

